### Study Design

A multicentre, single-blind, three-arm, randomized controlled trial will be conducted to assess the effect of reminiscence therapy combined with memory specificity training on improving autobiographical memory in older adults and further assess the effect on improving depressive symptoms in older adults. Based on the screening criteria, 78 participants will be recruited from three nursing homes in the provincial capital of China, and participants will be randomly divided into three groups in a 1:1:1 ratio. Participants in the first group will receive a 4-week intervention with reminiscence therapy, participants in the second group will receive a 4-week intervention with reminiscence therapy combined with memory specificity training, and participants in the third group will receive 4 weeks of usual care, followed by a 24-week follow-up.

Data will be collected at baseline, immediately postintervention, 1 month, 3 months, and 6 months postintervention. The study design is shown in Fig. 1. After the intervention, the same instructions will be given to a third group to ensure that more older adults benefit.

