### Participants

#### Eligibility and recruitment

Participants will be recruited from all three nursing homes simultaneously.

Once a nursing home has a sample of 26 subjects, they will proceed to the next step. Inclusion criteria are age ≥ 65 years; nursing home residence ≥ 3 months; Geriatric Depression Scale score ≥ 11; Mini-mental State Examination score ≥ 21; and voluntary participation in this study. Exclusion criteria include the acute onset of major illnesses such as cardiac, respiratory, digestive, or neoplastic disease; the development of a psychological illness other than depression; the taking of antidepressants or psychotropic drugs; an imminent discharge from a nursing home involved in the study; and receipt of other psychological treatment within the past 3 months.

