### Sample size calculation

Based on a priori power analysis (G-power3.1.9.7) using a power of 0.90 and error probability of 0.05, with a reference to a literature effect size of 0.8 [46, 47], a sample size of 24 participants per group will be needed. Assuming a 10% drop out rate, a sample size of 78 participants will be initially targeted.

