### Statistical analysis

A database will be established using EpiData, and the data will be entered by two persons and analysed statistically using SPSS 26.0 software. The measurement data such as scale scores will be expressed as the mean ± standard deviation (x ± s). Count data such as general demographic data will be described by the frequency and percentage. The status of each scale score before and after the intervention within each group and the measurement data between multiple groups will be analysed by repeated-measures ANOVA and simple effects analysis if they are normal and have equal variance, and the statistics will be described by median and mean difference (MD). For measures with skewed distribution, median and quartiles will be used to describe the statistics, and Kruskal‒Wallis multiple comparisons will be used to compare the data between and within groups. Intention-to-treat will be used to process the data and P < 0.05 will be considered statistically significant.

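### For skewed measures, the plan compares repeated scores within a group by Kruskal-Wallis, which assumes independent samples; the within-group tests are too conservative and miss real change

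*Protocol article*

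**What the plan says.** The Statistical analysis section of the protocol article sets out two branches.

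- **Normal data with equal variance.** Within-group and between-group data "will be analysed by repeated-measures ANOVA and simple effects analysis if they are normal and have equal variance". This branch recognises that the scores are repeated.
- **Skewed data.** The test named for this branch is Kruskal-Wallis, and its scope is given as "multiple comparisons will be used to compare the data between and within groups".

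The same paragraph shows what a within-group comparison is: "The status of each scale score before and after the intervention within each group". The Study Design section gives the assessments: "Data will be collected at baseline, immediately postintervention, 1 month, 3 months, and 6 months postintervention". Table 4 lists the depression, autobiographical memory, rumination and social engagement measures at all five.

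The significance rule is "P < 0.05 will be considered statistically significant". No paired or repeated-measures rank test is named anywhere in the article.

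**The concern.** Kruskal-Wallis compares independent samples. Between the three arms at one visit, each participant gives one score and falls in one sample. Within one arm across visits, each participant appears in all five samples. The differences between people are then counted as noise, although they cancel out of every within-person comparison. The reference distribution is wrong for such data, and a result reported as non-significant at 0.05 has been held to a much stricter standard.

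At stake are the plan's within-group statements for any skewed measure: whether scores in an arm changed after the intervention, and whether the change lasted to 6 months. The two branches are also inconsistent, because the repeated structure is respected in one and dropped in the other. This is not a detail left for an analysis plan. The article names a specific test for a specific comparison, and the test does not fit it.

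**Working it through.** **The plan's own figure.** The plan states no type I error or power for this branch, so there is nothing to reproduce. Its 24 participants per group is used below only as the number analysed; whether 24 follows from the sample size inputs is a separate question.

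**Inputs**

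- Participants in one group: 24 (Sample size calculation). Enrolment is 78/3 = 26 per arm.
- Visits: five, T0 to T4 (Study Design; Table 4).
- Nominal level: 0.05 (Statistical analysis).
- Within-person correlation: not given for the trial scores. Assumed 0.3 to 0.7 and equal for all pairs of visits. The article's only hint is a retest reliability above 0.73 for the depression scale. That points to the upper part of the range, although correlations over months of follow-up may be lower.
- Size of change: a sustained shift after T0 of 0.5 SD (assumed), and of 0.8 SD, which matches in number the effect size of 0.8 in the sample size section (its type is not stated there).

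**Step 1: type I error by approximation.** With no true change and equal correlation, the Kruskal-Wallis statistic for five visits behaves roughly like (1 − r_s) times a chi-square variable with 4 degrees of freedom, where r_s is the rank correlation between visits. For normal scores with correlation ρ, r_s = (6/π) × arcsin(ρ/2). The 5% critical value is 9.488, so the actual level is P(chi-square > x) with x = 9.488/(1 − r_s). For 4 degrees of freedom this equals exp(−x/2) × (1 + x/2).

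- ρ = 0.3: r_s = 0.288, x = 13.32, level = 0.0098
- ρ = 0.5: r_s = 0.483, x = 18.34, level = 0.0011
- ρ = 0.7: r_s = 0.683, x = 29.92, level = 0.000005

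**Step 2: type I error by simulation** (4,000 replicates per setting, 24 participants, five visits)

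| Correlation | Kruskal-Wallis | Friedman |
|---|---|---|
| 0 | 0.049 | 0.049 |
| 0.3 | 0.012 | 0.045 |
| 0.5 | 0.001 | 0.051 |
| 0.7 | 0.000 | 0.053 |

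The simulation agrees with the approximation. Its standard error at a true level of 0.05 is √(0.05 × 0.95/4000) = 0.003. With 26 participants Kruskal-Wallis gives 0.010, 0.003 and 0.000 at correlations 0.3, 0.5 and 0.7.

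**Step 3: power over five visits** (2,000 replicates; standard error at most √(0.25/2000) = 0.011)

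| Shift after T0 | Correlation | Kruskal-Wallis | Friedman |
|---|---|---|---|
| 0.5 SD | 0.3 | 0.27 | 0.41 |
| 0.5 SD | 0.5 | 0.18 | 0.55 |
| 0.5 SD | 0.7 | 0.11 | 0.78 |
| 0.8 SD | 0.3 | 0.76 | 0.84 |
| 0.8 SD | 0.5 | 0.75 | 0.95 |
| 0.8 SD | 0.7 | 0.74 | 1.00 |

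The scores were drawn as normal. Kruskal-Wallis and Friedman depend only on order, so the results are the same for any skewed score that is an increasing transformation of these, applied alike at all visits. Correlation and shift are therefore stated on the underlying normal scale, not on the skewed scale. Ties between whole-number scores were not modelled.

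**Step 4: two visits only.** For T0 against T1 with a 0.5 SD shift, the two-sample rank test (the two-sample form of Kruskal-Wallis) has power 0.35, 0.35 and 0.32 at correlations 0.3, 0.5 and 0.7. The Wilcoxon signed-rank test has 0.49, 0.62 and 0.86 on normal scores. Signed-rank power does change under transformation: on exponentiated scores it is about 0.57 and 0.77 at correlations 0.5 and 0.7. The direction is the same.

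**The case against.** The strongest reply is that little hangs on this. The hypothesis in the Background is mainly between arms, and Kruskal-Wallis across arms at one visit uses one score per person, so the dependence objection does not reach it. The error is conservative and creates no false claim of benefit. Most of this stands, and it limits the point to within-group tests in the skewed-data branch. It does not make the named test suitable for the comparison that the plan gives it.

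Several stronger readings are tempting, and the documents do not support them:

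- **A reader might infer that most of the power is always lost.** That holds for shifts of about 0.3 to 0.5 SD with correlation 0.5 or more. At 0.5 SD and correlation 0.3 the loss is from 0.41 to 0.27, and at 0.8 SD it is from 0.84–1.00 to about 0.75.
- **A reader might infer that every P-value from this branch is wrong.** The between-arm test at a visit is not affected. That it ignores baseline and gives no group-by-time test is a matter of efficiency and scope, not of validity.
- **A reader might infer from the entry rule, "Geriatric Depression Scale score ≥ 11", that the primary outcome is bound to fall in this branch.** The cut truncates only the baseline depression score. It does not cut later depression scores or the other three measures. The documents give no mean or SD. Assuming an untruncated mean of 11 to 18 and an SD of 4 to 5, a Shapiro-Wilk test on 24 baseline scores would reject in 8% to 68% of samples. How often the branch will be used is unknown.
- **A reader might infer that the main repeated-measures ANOVA must be replaced.** Nothing in this defect requires that. How skewness is to be judged is commonly left to the full protocol or analysis plan, which is not shown.

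One could also read the within-group wording as pairwise follow-up among the arms. The paragraph's own reference to scores before and after the intervention in each group speaks against that.

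**Conclusion.** The point holds in a limited form. As written, the fallback applies an independent-samples test to repeated scores of the same people. At a nominal 0.05, its actual type I error over five visits is about 0.01 at correlation 0.3 and close to zero at 0.5 or more. The cost in power runs from modest (0.84 to 0.76 at 0.8 SD, correlation 0.3) to severe (0.78 to 0.11 at 0.5 SD, correlation 0.7).

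That the test is mismatched follows from the text alone. The sizes rest on 24 participants with complete data, equal positive correlation in the assumed range, and a shift that appears at T1 and persists. The between-arm use is judged here only for dependence between repeated scores; other features of the allocation are not considered.

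**What to change.** In the Statistical analysis section, change the sentence on skewed measures so that:

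- Kruskal-Wallis is used only between the three arms, at a visit or preferably on change from T0.
- Within-group comparisons use the Friedman test over T0 to T4, followed by Wilcoxon signed-rank tests with a multiplicity adjustment (for example Holm over the four comparisons of T1 to T4 with T0).

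Friedman uses only participants with all five visits. With the planned 10% dropout that is about 26 × 0.9 = 23.4 per arm, close to the 24 used above. The sentence should say how incomplete participants are handled, since the section also promises an intention-to-treat analysis.

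The cost is one sentence of analysis wording. No further data, visits or participants are needed, and the normal-data branch stays as it is.

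### For skewed outcomes the plan compares visits within an arm by Kruskal-Wallis, an independent-samples test, so the within-arm P values come out too large

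*Protocol article*

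**What the plan says.** The Statistical analysis section of the protocol article has two branches. Scale scores, both before and after the intervention within each group and across groups, "will be analysed by repeated-measures ANOVA and simple effects analysis if they are normal and have equal variance". The other branch begins: "For measures with skewed distribution, median and quartiles will be used to describe the statistics". For that branch the plan adds that Kruskal-Wallis "multiple comparisons will be used to compare the data between and within groups". The threshold is the same throughout: "P < 0.05 will be considered statistically significant".

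The Study Design section states: "Data will be collected at baseline, immediately postintervention, 1 month, 3 months, and 6 months postintervention". Table 4 under Outcome measures lists the depression, autobiographical memory, rumination and participation measures at all five time points, T0 to T4. The article names no paired rank test.

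**The concern.** The section itself treats within-group analysis as the comparison of scores before and after the intervention in one arm. Those scores belong to the same people. Kruskal-Wallis and its post-hoc comparisons treat each visit as a separate sample, so 24 residents seen five times enter as 24 × 5 = 120 unrelated observations. Stable differences between residents then stay in the error term instead of being removed.

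The article names a particular test for a particular comparison, and the test does not fit, so this is not a detail left to a fuller document. The two branches also disagree: repeated-measures ANOVA respects the pairing, and its replacement for skewed data drops it.

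At stake are the within-arm statements on any skewed measure. The branch may well be used. Entry requires a depression score of at least 11 on a 0–30 scale, which cuts the baseline distribution from below, and the memory test yields small bounded counts. The article does not say that any measure will be skewed.

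**Working it through.** **Inputs from the article.** Five visits (Study Design; Table 4). 24 residents per arm (Sample size calculation: "a sample size of 24 participants per group will be needed"). Significance level 0.05. The article gives no power or error figure for within-arm comparisons, so there is none to reproduce. The 24 is used only as an input here.

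**Assumptions.** The article gives no planning value for within-person correlation. I use 0.3, 0.5 and 0.73. The last is anchored on the retest reliability reported for the depression scale (above 0.73). Correlation is taken as equal for all pairs of visits. Skewed scores are gamma with shape 2. Change is a drop after T0 held to T4, in SD units.

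**Step 1: direction of the error.** On ranks, H = (N − 1) × SS(visits) / SS(total), referred to chi-square with 5 − 1 = 4 degrees of freedom (critical value 9.488). If visits correlate at ρ, the variance of contrasts between visit means shrinks by the factor (1 − ρ), while the total spread hardly changes. Under no change, H therefore behaves roughly as (1 − ρ) times a chi-square on 4 df. The true error is P(chi-square > x) with x = 9.488 / (1 − ρ), and for 4 df this tail equals exp(−x/2) × (1 + x/2).

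- ρ = 0.3: x = 13.55, error ≈ 0.009
- ρ = 0.5: x = 18.98, error ≈ 0.0008
- ρ = 0.73: x = 35.14, error below 0.001

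The test rejects too rarely, not too often.

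**Step 2: simulation.** 10,000 replicates per cell, n = 24, skewed scores. Entries are rejection rates at 0.05, with Kruskal-Wallis first and the paired test second (Friedman for five visits, Wilcoxon signed-rank for two).

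| Setting | ρ = 0.3 | ρ = 0.5 | ρ = 0.73 |
|---|---|---|---|
| Five visits, no change | 1.0% / 4.5% | 0.2% / 4.7% | <0.1% / 4.6% |
| Five visits, 0.3 SD | 11.0% / 23.6% | 5.3% / 33.1% | 1.7% / 58.6% |
| Five visits, 0.5 SD | 42.5% / 59.0% | 35.8% / 76.3% | 28.0% / 95.1% |
| Five visits, 0.8 SD | 93.5% / 96.0% | 93.1% / 99.0% | 93.6% / 100% |
| T0 v T1, no change | 2.1% / 5.0% | 0.8% / 5.0% | 0.1% / 5.1% |
| T0 v T1, 0.5 SD | 51.8% / 55.4% | 52.0% / 69.1% | 53.8% / 90.4% |
| T0 v T1, 0.8 SD | 90.0% / 90.3% | 92.4% / 96.2% | 96.5% / 99.8% |

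At ρ = 0 Kruskal-Wallis holds its level (4.8%), which confirms that the correlation is the cause. A separate run of the five-visit case gave type I error of about 1.3%, 0.2% and below 0.1%, and power at 0.5 SD of 43%, 35% and 28% against 59%, 78% and 96%. The runs agree within two percentage points.

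**Step 3: sensitivity to shape.** With normal scores, five visits and 0.8 SD, Kruskal-Wallis power is 74–75% against 84–100% for Friedman over the same correlations. The small loss at 0.8 SD therefore depends on the assumed skewness, although skewness is what sends a measure to this branch.

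**The case against.** The strongest reply is that the defect is narrow and errs on the safe side. It sits in a conditional fallback and affects only its within-arm contrasts. The hypothesis in the Background compares the combined arm with usual care and with reminiscence therapy alone, so within-arm change is supportive. All of this stands, and it limits the severity. It does not make the named test fit the data.

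A reader might infer several stronger things that the documents and figures do not support:

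- **That most real within-arm change is missed.** This is not general. At 0.5 SD, T0 versus T1 is detected slightly more often than not. At 0.8 SD, the article's only planning effect (metric not stated, read here as SD units), skewed data lose little.
- **That power collapses as correlation rises.** It falls only in the five-visit test at smaller changes. For T0 versus T1 at 0.5 SD it is flat at about 52–54%. What grows is the gap to the paired test.
- **That wrong P values mean false positives.** The error runs the other way and cannot by itself create a spurious finding of benefit.
- **That relapse would be reported as maintained benefit.** The Background does hypothesise maintenance to 6 months, and a conservative T1-to-T4 test could be misread that way. But no loss between T1 and T4 was simulated, and the article does not say that a non-significant within-arm test will count as maintenance. No size can be put on this.

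A further fair objection concerns the remedy: Friedman needs every visit from each resident, which sits awkwardly with the stated intention-to-treat principle. That is taken up in the fix.

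**Conclusion.** The rule is wrong as written and should be corrected before analysis, but it does not undermine the trial's main comparison. Wherever a skewed measure is compared between visits within an arm, the stated test ignores the pairing and returns P values that are too large. The conservative direction needs only positive within-person correlation. The size depends on assumed correlations of 0.3 to 0.73, equal correlation between visits, 24 residents with all visits, and gamma-shaped scores. On those assumptions the five-visit type I error is about 1% or less, and a 0.5 SD change is missed in about 57–72% of trials, against about 4–41% with Friedman. For 0.8 SD the difference is only a few percentage points. Between-arm Kruskal-Wallis at a single visit and the repeated-measures ANOVA branch are not affected by this defect.

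**What to change.** Restrict Kruskal-Wallis to comparisons of the three arms at one visit. For skewed data within an arm, name the Friedman test across visits, with Wilcoxon signed-rank tests for pairs of visits and Holm adjustment.

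This takes one sentence. Both tests are available in SPSS, which the plan already uses, and no further data are needed. The cost lies in missing visits: Friedman uses only residents seen at all five. With 78 / 3 = 26 recruited per arm and the expected 10% dropout, about 26 × 0.9 = 23.4 would remain, and fewer if single visits are also missed. To stay close to the intention-to-treat principle, base the pairwise signed-rank tests on all available pairs, or replace both with a rank-based or mixed longitudinal model that uses every observed visit. The model takes more specification but removes the complete-visit restriction.

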**Methods:**

In this multicentre, single-blind, three-arm parallel randomized controlled study, we aim to enrol 78 older adults aged 65 years or older with a score of ≥ 11 on the Geriatric Depression Scale, and participants will be randomly assigned to either a reminiscence therapy group, a reminiscence therapy with memory specificity training group or a usual care group. Assessments will be conducted at baseline (T0) as well as immediately post-intervention (T1) and 1 (T2), 3 (T3) and 6 (T4) months post-intervention. The primary outcome measure is self-reported depressive symptoms, measured using the GDS. Secondary outcome measures include measures of autobiographical memory, rumination, and social engagement.

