Currently, reminiscence therapy combined with memory-specific training is mainly used in the psychological treatment of cancer patients in palliative care, and its effectiveness needs further validation, as randomized controlled trials of Life Review Therapy combined with Memory Specificity Training (LRT- MST) by Gitta Kleijn showed no significant differences between the two groups in terms of anxiety, depression, quality of life and autobiographical memory in cancer patients [41, 42]. However, other studies have shown that reminiscence therapy based on autobiographical memory training can be used in future studies to investigate available, cost-effective, low-intensity treatment options for patients experiencing mood disorders [43, 44]; thus, further investigation of this therapy is warranted.

Based on the national situation that depressed older people are increasing year by year in China, this study aims to implement a randomized controlled trial of reminiscence therapy combined with memory specificity training in a Chinese context to investigate whether this therapy can reduce rumination and improve depressive symptoms in older people and improve their psychological health by improving autobiographical memory. In this study, it is hypothesized that older people who participate in reminiscence therapy combined with memory specificity training will report improved autobiographical memory specificity, less rumination, and significantly lower levels of depressive symptoms at postintervention and follow-up time points than older adults receiving usual care and reminiscence therapy alone; we further hypothesize that these improvements will be maintained for 6 months after the intervention.

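### The GDS is primary without a primary visit or contrast, and one unadjusted 0.05 threshold covers two comparators at four visits, so a false claim is likelier than 5% if any significant result may be claimed.

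*Protocol article*

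**What the plan says.** - **Primary outcome** (Abstract, Methods): "The primary outcome measure is self-reported depressive symptoms, measured using the GDS". No visit is attached.
- **Visits** (Outcome measures, Table 4): the GDS is taken at baseline (T0), immediately after the intervention (T1), and at 1, 3 and 6 months (T2 to T4). The table ranks none of these above another.
- **Hypothesis** (Background, last paragraph): RT-MeST is expected to show significantly lower depressive symptoms "at postintervention and follow-up time points than older adults receiving usual care and reminiscence therapy alone". A further hypothesis, stated after this one, is that the gains last to 6 months.
- **Analysis** (Statistical analysis): repeated-measures ANOVA with simple effects, or Kruskal-Wallis multiple comparisons for skewed measures. The only threshold is "P < 0.05 will be considered statistically significant". The section does not make the simple effects conditional on a significant interaction.
- **Arms** (Study Design; Sample size calculation): "participants will be randomly divided into three groups in a 1:1:1 ratio", with 78 participants in total, that is 78/3 = 26 per arm.

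**The concern.** Two comparators at four post-baseline visits give up to eight GDS contrasts that bear on the hypothesis. The protocol does not say which one decides the trial, in what order they are read, or whether all of them must succeed. A report could therefore follow the stated rule to the letter and claim success from whichever contrast and visit fell below 0.05.

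The contrast most exposed is RT-MeST vs RT. It is the only one that shows whether memory specificity training adds anything to reminiscence therapy, and it can be read at four visits.

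**Working it through.** **Inputs from the protocol.** Three arms of 26; four post-baseline visits; two comparators for RT-MeST; threshold 0.05. Sidedness is not stated, so two-sided tests are assumed.

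**Inputs assumed.** The between-visit correlation is not given; 0.3 to 0.8, equal for all pairs of visits, is used. Participants are taken as independent and scores as normal.

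**Step 1: the nominal level.** One two-sided test at 0.05 has a 5% chance of a false difference, or 0.05/2 = 2.5% in favour of RT-MeST.

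**Step 2: the independence benchmark.**
- One comparator, four visits: 1 − 0.95^4 = 0.185.
- Two comparators, four visits: 1 − 0.95^8 = 0.337.

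The real tests are positively correlated, because visits share participants and both comparisons share the RT-MeST arm. The true figures are therefore lower.

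**Step 3: simulation with that correlation.** No arm differs from any other. Each contrast is a t-test at each of T1 to T4, two-sided 0.05, with 20,000 or more simulated trials per setting. The table shows the chance of at least one significant result.

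| Between-visit correlation | RT-MeST vs RT, either direction | RT-MeST vs RT, in favour of RT-MeST | Both comparators, either direction | Both comparators, in favour of RT-MeST |
|---|---|---|---|---|
| 0.3 | 17% | 9% | 30% | 15% |
| 0.5 | 16% | 8% | 27% | 14% |
| 0.7 | 13% | 7% | 23% | 11% |
| 0.8 | 12% | 6% | 20% | 10% |

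Allowing for variation between simulation runs, the ranges are about 11-18%, 5-9%, 20-30% and 10-16%. On change from baseline, the figures over both comparators are about 27% in either direction and about 14% in favour, whatever the correlation.

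**Step 4: would the ANOVA protect the contrasts?** Suppose the simple effects were read only after a significant group-by-time interaction.
- *All three arms equal:* the chance of any false difference over the eight contrasts falls to about 1-5%.
- *RT and RT-MeST both 0.8 SD better than usual care, and equal to each other:* with correlation 0.3 to 0.9, the interaction is significant in 70% to 100% of trials, because usual care differs. RT-MeST vs RT is then read at four visits. A false difference occurs in about 9-16% of trials, and one in favour of RT-MeST in about 5-8%.

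The second case is the one that matters for the added value of the training, and there the interaction test gives little protection.

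**The case against.** **The eight contrasts are inferred.** The Statistical analysis section names an ANOVA with simple effects, not a list of eight tests, and an analysis plan that is not shown may adjust or order them. This stands as a limit on the figures. It does not remove the point, because the missing visit for the primary outcome and the single threshold are in the protocol itself.

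**The hypothesis can be read jointly.** If RT-MeST had to beat both comparators at every visit, the error would be below 1%. If it had to beat both at the same visit, the error would be about 1-2% with all arms equal, but about 6-9% if RT works and the training adds nothing. The wording permits a joint reading, but no success rule adopts one.

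**Stronger readings the documents do not support.**
- A reader might infer that the trial's error rate simply is 20-30%. That holds only if any significant result may be claimed, counts differences against RT-MeST as well, and assumes no preliminary interaction test. The protocol commits to none of these.
- A reader might add RT vs usual care and count twelve contrasts. That comparison is not part of the stated hypothesis on RT-MeST.
- A reader might infer that all four visits have equal standing. Table 4 ranks none, but the Background sets 6-month maintenance apart as a further hypothesis.
- A reader might fault the sample size for having no allowance for multiple tests. That section does not name its test, and a fixed testing order at full 0.05 needs no such allowance.

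**Allocation.** Study Design describes randomising participants, while Randomization and blinding describes envelopes that decide which nursing home delivers which intervention. If arm and home coincide, calculations for independent participants do not give the trial's true error rate. This stands, and it limits both the figures and what the fix can achieve.

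**Conclusion.** The point holds in conditional form. The primary outcome lacks a primary visit and a primary contrast, and the one decision rule does not say how several GDS results combine into a conclusion.

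If any significant visit may be claimed, the chance of wrongly concluding that the training adds to RT is roughly two to almost four times the 2.5% of a single test (5/2.5 = 2; 9/2.5 = 3.6). Over both comparators, the chance of a false claim in favour of RT-MeST is roughly four to six times that level (10/2.5 = 4; 16/2.5 = 6.4).

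These sizes rest on the assumed correlation, two-sided tests, 26 independent participants per arm, and no adjustment. A joint success rule or an adjustment set elsewhere would reduce or remove the inflation. A preliminary interaction test would do so only when all arms are equal.

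**What to change.** Name one primary GDS visit. T1 is a natural example, because the Background states the post-intervention benefit before 6-month maintenance, but the choice is the sponsor's. Then test in this order, each at two-sided 0.05 and only if every earlier step is significant:

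1. RT-MeST vs usual care at T1
2. RT-MeST vs RT at T1
3. RT-MeST vs usual care at T4
4. RT-MeST vs RT at T4

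Steps 3 and 4 must be ordered. Two contrasts at one visit, each at 0.05, carry about 9% error between them. Report T2, T3 and the secondary outcomes as estimates with confidence intervals, labelled supportive.

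**Cost.** A few sentences in the Statistical analysis section, no extra participants, and no splitting of the 0.05. T2 and T3 can carry no confirmatory claim, and RT-MeST vs RT is tested only if the first step succeeds.

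**Limit.** This controls multiplicity only. The conflict between randomising participants and allocating whole nursing homes must be reconciled separately.
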